##### GD-RL behavioral and connectivity imaging indicators

The behavioral (model-based weighting parameter ω) and connectivity imaging indicators (CEN-SN activation difference) will be used as potential mediating factors to determine whether behavioral and imaging indicators could explain the changes in depressive and/or anhedonic symptoms. Within-group explorative analysis will be conducted using a stepwise regression using a bootstrapping test when multiple mediators are concerned (46) with PROCESS macro (http://www.afhayes.com/) of SPSS 22.

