Neurofeedback based on real-time functional magnetic resonance imaging (rt-fMRI) uses measured changes in brain activation to help participants regulate activity in selected regions or networks. During rt-fMRI neurofeedback, participants are provided with visually presented brain network activation information in real time (24). The rt-fMRI neurofeedback targeting the brain areas within SN involved in emotion processing (e.g., amygdala, insula, and striatum) decreased the anhedonic or depressive scores (25, 26). However, the effects of rt-fMRI neurofeedback (NF) based on CEN-SN on anhedonia to the best of our knowledge have not been investigated previously. Network-based NF can be used to recalibrate the balance between brain networks (27). It has been recommended that researchers use NF methods that consider neural response across regions (i.e., functional connectivity) (28). Recent studies have found that participants can flexibly regulate the balance between the CEN and SN through rt-fMRI neurofeedback which could promote resilience to stress (29). Therefore, the use of rt-fMRI neurofeedback to improve goal-directed reward learning is a potential intervention that involves the interaction between CEN and SN. Additionally, reward learning studies have typically adopted computational modeling during behavioral tasks to estimate expected value and reward prediction errors (RPEs) (20). Therefore, the current study was designed to adopt reward learning tasks (30) and computational modeling in anhedonic individuals to examine goal-directed brain network dynamics. Network-based rt-fMRI neurofeedback will be utilized to improve the balance of CEN/SN within the goal-directed brain network (Figure 1). The within-group changes of depressive symptoms after rt-fMRI NF training of goal-directed brain network will be examined to assess the effects of rt-fMRI NF intervention to improve depressive and/or anhedonic symptoms for depressed patients. The goal-directed RL, as well as CEN/SN changes (CEN-SN functional connectivity) at 3- and 6-month follow-ups, will also be examined to evaluate the long-term rt-fMRI neurofeedback training effects. This study may provide evidence to elucidate the effect of rt-fMRI NF based on the goal-directed system in alleviating depressive/anhedonic symptoms. The rt-fMRI NF training may have clinical implications with improved safety and minor side effects (31).

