#### Pre- and post-test

Before and after the neurofeedback intervention, the primary and secondary outcome measures of the depressive and anhedonic symptoms will be assessed in all subjects. The behavioral tasks will be repeated post-training to evaluate the NF training effect on goal-directed behavior. The follow-up assessments include the primary outcome of depression and secondary outcome of anhedonia, the goal-directed RL (model-based weighting parameter ω), and the CEN-SN functional connectivity (Pearson's correlation) based on prediction errors (PEs) (Figure 2).

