##### Self-regulation performance

For each subject in the patient group in each session, self-regulation performance will be assessed with the CEN-SN activation difference (computed through online time courses of ROIs extracted using Turbo-BrainVoyager) during the training. Self-regulation performance will be defined as the mean % signal change of ROIs (CEN and SN) over all the NF runs. The self-regulation performance will then be submitted to an ANOVA with the factors group (NF vs. YC) and session (four sessions) for the group and/or time effects of rt-fMRI NF training.

Additionally, to investigate the pre- and post-training difference in CEN-SN functional connectivity for each patient group, we will apply the paired *t*-tests or Wilcoxon signed-rank tests (depending on parametric or non-parametric distributions) between the pre- and post-training tests, while undergoing MDT behavioral task during neuroimaging.

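### The mediation analysis is specified only within group, so it cannot show that neurofeedback acted through ω or CEN/SN, and its imaging mediator is an activation difference labelled as connectivity

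*Protocol article*

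**What the plan says.** The section on GD-RL behavioral and connectivity imaging indicators gives the purpose as "to determine whether behavioral and imaging indicators could explain the changes in depressive and/or anhedonic symptoms". The mediators are ω and an imaging quantity: "connectivity imaging indicators (CEN-SN activation difference) will be used as potential mediating factors". The method is "Within-group explorative analysis will be conducted using a stepwise regression using a bootstrapping test when multiple mediators are concerned", using the PROCESS macro in SPSS. No independent variable is named.

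The imaging measure is described differently elsewhere:

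- Introduction: "CEN/SN changes (CEN-SN functional connectivity) at 3- and 6-month follow-ups".
- Pre- and post-test: the follow-up measure is "the CEN-SN functional connectivity (Pearson's correlation) based on prediction errors (PEs".
- Self-regulation performance: "self-regulation performance will be assessed with the CEN-SN activation difference", taken from online time courses during training, and "Self-regulation performance will be defined as the mean % signal change of ROIs (CEN and SN) over all the NF runs". The same section then tests functional connectivity before and after training, during the decision task, as a separate analysis in each patient group.

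The section on the neurofeedback procedure randomises 40 patients 1:1, 20 to NF and 20 to YC. The primary and secondary outcome analyses compare NF with YC.

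**The concern.** To say that neurofeedback worked through an indicator, one must show that it moved the indicator and that the indicator carried the effect to symptoms. The first step needs a contrast between patients who received real feedback and patients who did not. The trial has that contrast, but the mediation analysis as written does not use it.

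The Discussion lists practice, placebo and natural change as alternative sources of benefit and adopts the yoked control for this kind of reason. A within-arm analysis sets that control aside at the step where mechanism is inferred. A positive result could then be reported as evidence of mechanism when it shows only that patients who improved more also had higher values on the indicator.

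The labelling adds a second problem. If one section's connectivity indicator is an activation difference and another's is a correlation, a reader cannot tell which quantity was tested as mediator, or whether it was measured before the symptom score it is meant to explain.

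**Working it through.** The article gives no effect size, significance level or power for the mediation, so there is no planned figure to reproduce. The only relevant numbers are the group sizes: 20 + 20 = 40, which agree.

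**1. What can be estimated within one arm.** Let X be the group (NF = 1, YC = 0), M the mediator and Y the symptom score.

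- M = i₁ + aX + e
- Y = i₂ + c′X + bM + e
- indirect effect of NF = a × b

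In the NF arm X = 1 for all 20 patients. The columns for the intercept and X are identical, so the design matrix [1, X] has rank 1. Only the sum i₁ + a is identified, and neither a nor a × b can be estimated. With both arms (n = 40) the rank is 2 and a becomes estimable. Within an arm only b, the mediator-symptom association, is left.

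**2. How easily that association appears without any NF effect.** The inputs are n = 20 per arm (stated), and a two-sided 5% level and correlations of 0 to 0.7 between patients' mediator and symptom values (both assumed). The critical |r| is t/√(18 + t²) with t = t(0.975; 18), which gives 0.44. In 10,000 simulated trials with no NF effect on mediator or symptoms:

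| Assumed correlation | Within-NF association significant | Two-arm test, a and b both significant |
|---|---|---|
| 0 | 4.8% | 0.3% |
| 0.3 | 25.6% | 2.0% |
| 0.5 | 64.5% | 4.4% |
| 0.7 | 95.5% | 4.9% |

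The Fisher-z approximation, Φ(√17 × atanh r − 1.96), agrees: 0.25 at r = 0.3 and 0.62 at r = 0.5.

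The middle column is the power to detect a real association. It is not a type I error rate for that association. It matters because the association can be real while NF has done nothing. A common average recovery is not enough to produce it: recoveries must covary from patient to patient.

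**3. Whether the two imaging measures are interchangeable.** For network time courses C and S and any constant k, mean(C + k) − mean(S) rises by k, while corr(C + k, S) = corr(C, S). Simulated series of 250 points (an assumed length; separate draws, so r varies by sampling) show this:

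| True correlation | Mean difference 0: sample r | Mean difference 1: sample r |
|---|---|---|
| −0.5 | −0.495 | −0.488 |
| 0 | 0.010 | 0.016 |
| 0.5 | 0.449 | 0.526 |

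Either mean difference can occur with any of the correlations. An activation difference and a Pearson correlation are different quantities.

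**4. Precision after the change.** With 20 per arm, 80% power for the path from group to mediator needs a standardised difference of (1.960 + 0.842) × √(2/20) = 0.89. Power is about 35% at 0.5 and 72% at 0.8.

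**The case against.** **The analysis is exploratory.** It is labelled so, the Discussion concedes limited power and non-specific training effects, and HAMD-17 and SHAPS are compared between arms. This stands and limits the consequence. The label lowers the strength of the claim, but it does not change what is estimated.

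**Aim 2 does not rest on this analysis.** A reader might infer that the second aim fails. As worded, it concerns the effects of neurofeedback on the indicators, and the Self-regulation performance section plans an ANOVA of NF versus YC by session for the activation difference. The stronger reading is not supported.

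**A within-arm model is possible.** Time (before to after training) could serve as the independent variable, and the Introduction says that within-group symptom change will be examined. But no such model is described, and it would mix NF with the non-specific changes. It would be too strong to say that nothing can be modelled within an arm. What cannot be isolated there is an effect of NF.

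**The word stepwise is ambiguous.** One might infer automatic selection of the best-looking mediator. Paired with a bootstrap test and PROCESS, it may mean causal-steps or hierarchical regression. The wording needs clarifying, and the main point holds under either meaning.

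**The activation difference might be available outside training.** A reader might conclude that it is never measured at pre-test or follow-up. The documents do not say that. Task imaging is planned before and after training, and the quantity could be derived from it. What can be said is that the mediator's measurement time is not stated.

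**The activation difference is a natural mediator.** The feedback is built on the CEN-SN differential signal, so this is the quantity being trained. That stands: nothing here requires replacing it with connectivity.

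**Conclusion.** The point holds. As written, the mediation analysis can show only an association between indicator and symptoms in about 20 patients per arm. It cannot show that NF acted through ω or CEN/SN. This follows from the design and needs no numerical assumption.

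The illustrative size, 26% to 64% significant within-arm associations with no NF effect, rests on assumed correlations of 0.3 to 0.5 for which the documents give no support. A reader might take it as a false-positive rate of the planned test, but it is not one.

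The labelling conflict is plain on the text: the mediation section calls an activation difference a connectivity indicator, while three other places use functional connectivity as a separate measure. ω is named consistently, so the conflict concerns the imaging mediator only.

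The plan should be changed here, but the matter is of moderate weight. It affects an exploratory analysis of mechanism and leaves the primary HAMD-17 comparison untouched.

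**What to change.** - Run the exploratory mediation on all 40 randomised patients with NF versus YC as the independent variable.
- Enter the prespecified mediators together, without data-driven selection, and replace or define the word stepwise.
- Adjust for the baseline symptom score, and for the baseline mediator where one exists. Report bootstrap intervals for each indirect effect.
- Name one imaging mediator, either the activation difference or the Pearson connectivity, and label it correctly. State when it is measured, at a time before the outcome it is meant to explain. An activation difference taken during training precedes the post-test scores; a connectivity measured at post-test would need a later symptom assessment. Use the same term in the Pre- and post-test, Self-regulation performance and mediation sections.
- Keep any within-group regression as description only.

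The cost is a change of analysis wording, with software and data already planned. The intervals will be wide at n = 40. Randomisation protects the path from group to mediator but not the path from mediator to symptoms, so the result should still be reported as exploratory.

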## Discussion

The deficits in RL represent a sub-phenotype of anhedonia, with partially separable neural substrates (47). The decision-theoretic view of depression favors the compromise of the GD system, rather than the habitual system in depression (48), the former of which is present in both behavioral and neural manifestations during RL for clinical and subclinical depression (5, 7, 49). Acute stress affects the allocation of neural resources within large-scale brain networks, especially the balance between the CEN/SN in the GD system due to cognitive demands (50). Additionally, the acute stress (during the last month) is supposed to trigger shifts in goal-directed vs. habitual behavior pattern, which is concomitant with specific network configurations, especially frontostriatal circuits (CEN: LPFCal SN: VTA/putamen/caudate↓, lateral/medial OFC↓) (7). Stronger PEs may contribute to highly variable momentary mood fluctuations due to stronger reward feedback dynamics, whereas the influence of PEs on RL is compromised in depressed individuals (51). In summary, these studies highlight a promising target for RL-based NF interventions for anhedonic depression to produce flexible mood changes. Moreover, the focus on the GD-RL and imaging substrates in the current protocol may provide more insights with regard to the factors driving NF outcomes (38).

The novelty of the current study is that we focus on neither single ROI nor functional connectivity limited to a few ROIs, but rather the balance between two functionally intertwined brain networks (CEN/SN), and this approach has been utilized in self-regulation and sustained attention (27, 29). However, the impact of network-based NF on reward learning is still unknown. Thus, we propose to simultaneously decrease CEN and increase SN activity (CEN: LPFC↓; SN: VTA/putamen/caudate↑, lateral/medial OFC↑), which could potentially improve mood and its fluctuations. Individualized NF training based on a goal-directed subnetwork is potentially advantageous for improving treatment response to anhedonia symptoms for depressed patients.

Additionally, the current study takes into account the potential confounding factors of motivation and demand characteristics. The mechanism underlying NF may come from NF-specific or non-specific contextual factors as well as general non-specific effects such as practice, placebo, and natural change (cognitive development or decline)(38). Therefore, a double-blind yoke-controlled design is adopted in this study to control for individual differences in motivation and effort. As a limitation, insufficient power may result from the limited sample size. To control for inter-subject variance, yoke-controlled NF will be provided for the participants to modulate the fMRI signals, in which sham feedback has been shown to regulate neural activity in cognitive control compared to passively viewing conditions (52).

The caveat of this study is the use of CEN and SN based on intermittent, rather than continuous imaging feedback signals, due to the signal calculation speed of network parameters and the high cognitive load of momentary feedback (53). Accumulating evidence indicates that intermittent feedback is more efficient than continuous feedback to reinforce the participants' internal thoughts (54, 55). However, other studies showed that continuous feedback improved regulation ability (56). Additionally, monetary reward elicits a greater extent of self-regulation than non-reward feedback (57). Therefore, further study would be able to determine the influence of intermittent vs. continuous feedback and trial-by-trial virtual monetary reward on GD-RL, though the monetary reward in this study is not contingent on participants' decision as in the Markov decision (MD) task. Feedback design for NF training should be carefully considered in future research.

Finally, accumulating evidence converges on the feasibility and effectiveness of frontostriatal connectivity as NF targets (58). Within SN, the lateral and medial part of OFC as well as ACC densely project to the dorsal (e.g., caudate) and ventral striatum, which are involved in goal-directed control of instrumental actions (59). Moreover, the clinical efficacy of NF targeting both emotion areas and higher visual areas may indicate the non-specific training effects of NF, e.g., the brain control and reinforcement components (25). Therefore, confounds from the non-specific training effects should be taken into consideration during the explanation of the results. Additionally, further empirical studies and systematic reviews may shed light on the most efficient NF targets and provide more evidence on NF targeting specific ROIs of CEN/SN and connectivity-based and network-based NF within the GD-RL systems.

## Ethics statement

The study was reviewed and approved by the ethical review committee at the Army Medical University (AMU, PRC). Written informed consent to participate will be obtained from participants.
